### Sample size

Power calculations indicated that 90 adolescents per condition (assuming an alpha of 0.05, 0.95 power, and a medium effect size, based on power calculations of G*Power (Faul et al. 2009)), are sufficient to detect a difference in problem behaviour at post-test. There is also sufficient power to perform moderator-analyses for different subgroups (Power > .80 to detect small effects for 2 to 8 groups). Therefore, a total of 180 adolescents and parents will be included.

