### Instruments

Table 1 shows the concepts, sources, and times of assessment for all used instruments. Most questionnaires will be administered at all measurement moments, except for the questionnaires of *intelligence*, *client satisfaction*, *motivation*, *therapeutic alliance* and *moral reasoning*. The questionnaires concerning treatment can only be filled out during the intervention phase (T2 en T3). The other two questionnaires (intelligence and moral reasoning) are filled out at one or two assessment moments in order to avoid overcharge of the respondents.

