### Statistical analysis

Primary analyses will be performed according to the intention-to-treat principle (Montori & Guyatt 2001). The effect of the intervention with regard to the difference in official arrest rates (recidivism) between the experimental and control group will be examined using logistic regression analysis and survival analysis. The primary (involvement in delinquency, SRD) and secondary continuous measures will be analyzed with ANCOVA using the outcome measures at post-test and follow-up as dependent variables, treatment condition as factor and pre-test scores as covariates.

Moderator analyses will be conducted using two-way ANCOVA’s with the moderators and treatment condition as factors, to examine interaction effects. For each questionnaire, the effect size is computed as Cohen’s *d*, based on adjusted means and standard errors, with a positive sign indicating improvement in the NP group relative to the control group. Mediator effects will be analyzed using structural equation modelling.

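### Cohen's d built from ANCOVA-adjusted means and standard errors points to the residual SD, which makes d larger than the conventional value by a factor that varies with the pre-test correlation

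*Protocol article*

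**What the plan says.** The Statistical analysis section of the protocol article analyses the self-reported delinquency score and the continuous secondary measures by ANCOVA. Post-test and follow-up scores are the dependent variables, with "treatment condition as factor and pre-test scores as covariates".

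The effect size follows in the next paragraph. Its scope is every questionnaire ("For each questionnaire, the effect size is computed as" Cohen's d), and it is "based on adjusted means and standard errors, with a positive sign indicating improvement in the NP group relative to the control group". The section gives no conversion formula and does not name the SD that forms the denominator.

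Table 1 shows that most scales are measured at T1, so most have a pre-test score to adjust for. It marks client satisfaction (C-toets) and therapeutic alliance (TASC) at T2 and T3 only, and intelligence (GIT) at T4 only. For the treatment scales the Instruments section agrees: "The questionnaires concerning treatment can only be filled out during the intervention phase (T2 en T3"). Motivation (VMB) is unclear, because that sentence covers it while Table 1 also marks it at T1.

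**The concern.** A conventional Cohen's d divides a mean difference by the SD of the outcome scores. The standard error of an ANCOVA-adjusted mean rests instead on the residual mean square, that is, on the variation left after the pre-test has explained its share. An SD recovered from such a standard error is smaller than the outcome SD, and the resulting d is larger. How much larger depends on how strongly the pre-test predicts the outcome.

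Three things are at stake:

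- **Between scales.** The article lists many questionnaires. For the same true effect, the more stable scale would show the larger d.
- **Between time points.** T3 is 6 months after T1, and T4 is 12 months after T3. If the correlation with T1 weakens over that time, d shrinks at follow-up even when the effect is constant. The Discussion hopes to detect effects that emerge late, so the comparison over time matters.
- **With other work.** A value labelled Cohen's d will be set beside values from other studies that used a raw SD.

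**Working it through.** **Inputs.** Outcome model and effect-size ingredients: Statistical analysis. Group size of 90 per arm: Sample size. Assessment times: Design and Table 1. Correlation r between pre-test and outcome within arms: not given, so assumed from 0 to 0.8.

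**The plan's own figure.** The article states no figure for the effect-size conversion, so there is nothing to reproduce on this point. Only the 90 per arm is used below.

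**Step 1: what the standard error contains.** For arm j with n participants,

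SE(adjusted mean) = s_res × sqrt(1/n + (xbar_j − xbar)²/SSx),

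where s_res is the residual SD and x is the pre-test. After randomisation the second term is small, so SE × sqrt(n) ≈ s_res. The standard error of the adjusted difference leads to the same place: SE(difference) ≈ s_res × sqrt(2/n), so SE(difference) × sqrt(n/2) ≈ s_res.

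**Step 2: residual SD against outcome SD.** s_res = SD × sqrt(1 − r²). Hence

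d from adjusted SEs = d from raw SD × 1/sqrt(1 − r²).

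**Step 3: numbers.** The formula was checked by simulation with 90 per arm, a true d of 0.50 and 3,000 trials for each r. The SD came from SE × sqrt(n) in one calculation and from the unadjusted pooled within-arm outcome scores in the other.

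| Assumed r | 1/sqrt(1 − r²) | Mean d, SD from adjusted SEs | Mean d, raw SD | Simulated ratio |
|---|---|---|---|---|
| 0 | 1.000 | 0.495 | 0.496 | 0.999 |
| 0.3 | 1.048 | 0.521 | 0.498 | 1.047 |
| 0.5 | 1.155 | 0.573 | 0.497 | 1.154 |
| 0.6 | 1.250 | 0.627 | 0.502 | 1.250 |
| 0.7 | 1.400 | 0.705 | 0.504 | 1.401 |
| 0.8 | 1.667 | 0.838 | 0.504 | 1.666 |

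The raw-SD version stays at about 0.50 for every r; the other version rises with r.

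**Step 4: what this does to comparisons.** Take a true d of 0.40 throughout.

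- Two scales at one time point, r = 0.3 and r = 0.7: 0.40 × 1.048 = 0.42 and 0.40 × 1.400 = 0.56.
- One scale at two time points, r = 0.7 at T3 and r = 0.5 at T4: 0.40 × 1.400 = 0.56, then 0.40 × 1.155 = 0.46. The decline is produced by the denominator alone.

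**Step 5: where it does not apply.** C-toets, TASC and GIT have no T1 score, so there is no pre-test of the same scale to shrink the residual. For a scale with r near 0 the factor is near 1.

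**The case against.** The strongest reply is that the article names no denominator. The investigators hold the raw data and could standardise by a raw SD, and a condensed article may leave the formula to a fuller document. This stands in part: use of the residual SD is an inference. It is still the natural reading, because the standard error is the only measure of spread the sentence supplies. If a raw SD is intended, the sentence misdescribes the method and needs the same correction.

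A second reply is that standardising by the residual SD is legitimate and that the choice of standardiser is partly convention. That is fair if the result is labelled as such. It does not make the result comparable with a conventional d. A T1 SD is not beyond criticism either: the sample is selected for problems, and a restricted range at T1 could itself raise d.

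Third, no r is documented, so a material distortion is possible but not shown. At r = 0.3 a d of 0.40 becomes only 0.42. This also stands, and the size can be given only as a range.

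A reader might infer more than the article supports:

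- **That every effect size is inflated.** This fails for scales without T1 and for scales with r near 0.
- **That the standard error itself is the divisor.** In the simulation this gave values of about 4.7 to 8.0 for a true d of 0.5. The article does not say it, and it is not a sensible reading.
- **That d conflicts with the planning assumption.** The Sample size section says only "assuming an alpha of 0.05, 0.95 power, and a medium effect size". It gives no numeric effect and no SD, so it cannot be shown which scale that effect is on.

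**Conclusion.** The point holds in a conditional form. Followed as worded, the recipe gives a d that exceeds the conventional raw-SD value by 1/sqrt(1 − r²) for any scale adjusted for a correlated pre-test. The excess is nil at r = 0, about 5% at 0.3, 15% at 0.5, 40% at 0.7 and 67% at 0.8. All these values of r are assumptions. Because r can differ between questionnaires and between T3 and T4, the reported values would not be comparable in either direction.

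The conclusion rests on reading the stated ingredients as the source of the denominator. The excess is relative to a raw-SD d only. The adjusted mean differences, the ANCOVA tests and their p-values are unaffected, as are the logistic and survival analyses of recidivism. This is a fault in a descriptive summary. It should be corrected because that summary is planned for each questionnaire and carries a label with a settled meaning.

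**What to change.** Replace the wording on adjusted means and standard errors with a definition that names the denominator:

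- d is the ANCOVA-adjusted mean difference divided by the pooled unadjusted within-arm SD at T1. The same SD is used for T3 and T4, so that a change in d over time reflects a change in the difference.
- For scales without a T1 score, use the pooled raw SD at the assessment concerned and label those values as such, since they are not on the same footing. Settle whether motivation has a T1 score, because the Instruments text and Table 1 differ.
- Report the 95% CI by dividing the limits for the adjusted difference by the same SD. This treats the SD as known and should be stated.
- Keep the sign convention.

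The change takes a few sentences and uses data already planned for collection. Its cost is that reported effect sizes become somewhat smaller wherever the pre-test predicts the outcome.

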## Discussion

This article describes the study protocol of a program evaluation of the prevention program ‘New Perspectives’ (NP). This study is one of the few randomized clinical trials in Europe examining a program targeting youth at risk for the development of a persistent criminal career (Farrington & Welsh 2005). By conducting an experimental research strategy (RCT) we will be able to control for confounding effects more accurately than in studies with other designs. Furthermore, there are several strengths with regard to the design of the present study.

First, this evaluation study is carried out in the routine youth care practice, which contributes to the ecological validity of the findings. In addition, the use of an active control condition (care as usual) under real life conditions gives more insight in the unique contribution of NP compared to standard youth care interventions. This information is crucial for practitioners, policy makers and politicians in order to determine which prevention programs can best be implemented.

A second strength is the examination of potential moderators and mediators. We focus on moderators, such as ethnicity, age and gender. Moderator analyses establish under which circumstances interventions are effective in reducing problem behaviour (Clingempeel & Henggeler 2002). Through this method we could detect whether NP is effective with older or younger adolescents, boys or girls, and with adolescents from different ethnic backgrounds. Further, our study includes diverse secondary outcome measures (e.g., cognitive distortions) leading to a better understanding of processes that could mediate the relation between the intervention and delinquent behaviour.

Third, when examining the effects in terms of delinquent behaviour we distinguish between involvement in, frequency and seriousness of delinquent acts. These specific measures of criminal offending contribute to a more detailed view on program effectiveness (Farrington & Welsh 2005). Moreover, the investigation of long-term effects up to one year after the intervention could identify possible sleeper effects.

Finally, the role of general treatment factors, such as the therapeutic alliance, are also taken into account. This will lead to a better understanding of the influence of non-specific treatment factors on the program effects, and the unique effects of specific treatment factors over non-specific treatment factors.

Despite these strengths several pitfalls of this study design should be mentioned. One of the greatest challenges in conducting randomized experiments is avoiding drop-outs of respondents. In order to decrease the risk of drop-outs, we will apply a pre-randomization trial. The randomization will be conducted before active informed consent of respondents, which promotes random allocation and improves inclusion of participants. As a consequence, we need full cooperation of all referral institutions in providing sufficient information about the effect study before randomization. Therefore, we will actively inform all referral institutions in Amsterdam about the research design. In order to gain full cooperation of all institutions, we will start informing management staff of the most important youth care organizations in Amsterdam. Next, all involved institutions will receive detailed instructions about the study design through presentations of the researchers (on local levels).

Furthermore, in order to avoid drop-out during the research period, we will minimize efforts of youths and their parents through the application of online questionnaires. Researchers will visit respondents in their own environment (at school, at home, etc.). The youth care workers will facilitate the assessments by inviting researchers directly after their client appointments. At first assessment, youths and parents will be clearly informed about the importance and content of the study.

A final important risk of the present study design concerns the use of an active control condition (care as usual). Comparing NP to an active control condition (of other standard interventions) may lead to an underestimation of the mean effect size. The heterogeneous nature of the CAU condition and the possible evidence-based treatments (e.g., CBT) within this condition could result in a lower mean effect size. This methodological problem will be reduced by increasing the power.

## Conclusion

The present study will provide more insight in the effects of the prevention program ‘New Perspectives’ (NP) on a broad range of outcomes. More specific knowledge will be obtained about potential mediators of the effectiveness of NP, the role of non-specific treatment factors and the effects for different subgroups of youngsters. This information will contribute to improvement of programs for juveniles at risk for the development of a persistent criminal career.
